| 

</

 |           |         |         |          |          |                 |        |        |        |         |           |           |            |             |            |             |                           |

1. The informed consent form must be signed before any study-related procedures are performed.

2. Vital signs include supine blood pressure, respiration, pulse, and SaO2.

3. Urinalysis with microanalysis: Urinary protein, glucose, ketones, hemoglobin, bilirubin, pH, specific gravity; Micro: red blood cells, white blood cells, epithelial cells, casts, crystals.

4. Complete blood count (CBC): Red blood cell (RBC) with mean corpuscular volume (MCV), mean corpuscular hemoglobin (MCH), mean corpuscular hemoglobin concentration (MCHC); hemoglobin, hematocrit, white blood cell (WBC) count [with differential % neutrophils, lymphocytes, monocytes, eosinophils, and basophils], absolute neutrophil count, and platelet count
5. Serum chemistry: Sodium, potassium, total protein, bicarbonate, chloride, BUN, GGT, creatinine, glucose, calcium, SGOT, SGPT, alkaline phosphatase, total bilirubin, albumin
6. Serum lipids: fasting total cholesterol, HDL, LDL, triglycerides
7. Patient takes thyroid protection medication each day on Days -24 hrs through Day 14.
8. Pharmacokinetic analysis (PK) samples: One EDTA (lavender top) tube; processed per instructions from Covance
9. Biodistribution samples: One EDTA (lavender top) tube; processed in nuclear medicine department (or designee)
10. Whole body imaging may be obtained 15-35 minutes post injection on Day 0.
11. At the Investigator's discretion, optional SPECT imaging may be obtained between Days 3 and 14
12. Total urine collection: Collected and analyzed in the nuclear medicine department (or designee.) Patient is given containers for each time period, in the following increments: 0-24 hrs [Day 0-Day 1]; 25-48 hrs [Day 1-Day 2]; 49-72 hrs [Day 2-Day 3]; 73-96 hrs [Day 3-Day 4]; 97-144 hrs [Days 4-6]; Days 6-10; Days 10-14.

\*\* Final Visit

## 8.2 STUDY EVALUATIONS

### 8.2.1 Screening Period

The screening evaluation will include a complete medical and medication history, physical and laboratory examinations (CBC, serum chemistry and urinalysis), ECG, verification of the criteria for a diagnosis of cancer, documentation of previous therapy for malignancies and a pregnancy test (if female of childbearing potential). All patients must provide informed consent prior to any procedures being done for the study and must satisfy the entry criteria.

#### **Within 7 Days Prior to the Day of Treatment**

- Signed Informed Consent Form (Consent must be obtained prior to performance of any study specific tests or evaluations)
- Demographics (age, gender, race and ethnicity if applicable)
- 12-lead electrocardiogram (ECG)
- Body weight and height
- Assessment of Eastern Cooperative Oncology Group (ECOG) performance status
- Histological or cytological confirmation of cancer (at any time in the past)
- Collection of medical history and list of current medications
- Documentation of previous treatment for malignancies
- Physical examination
- Temperature, vital signs (supine blood pressure [BP], pulse, respiratory rate), and pulse oxygen saturation (SaO2)
- Urinalysis with microscopic analysis: urinary protein, glucose, ketones, hemoglobin, bilirubin, pH, specific gravity, red cell count, white cell count, epithelial cell count, casts, crystals.
- Complete blood count (CBC): Red blood cell (RBC) with mean corpuscular volume (MCV), mean corpuscular hemoglobin (MCH), mean corpuscular hemoglobin concentration (MCHC); hemoglobin, hematocrit, white blood cell (WBC) count [with differential % neutrophils, lymphocytes, monocytes, eosinophils, and basophils], absolute neutrophil count, and platelet count
- Serum chemistry: Sodium, potassium, total protein, bicarbonate, chloride, blood urea nitrogen (BUN), Gamma Glutamyl Transferase (GGT), creatinine, glucose, calcium, Serum Glutamic-Oxaloacetic Transaminase (SGOT), Serum Glutamic Pyruvic Transaminase (SGPT), alkaline phosphatase, total bilirubin, albumin

### 8.2.2 Treatment Period

#### **Day -1 (24 hrs Pre-Dose)**

- Patient takes thyroid protection medication.
- Serum pregnancy test in female patients of childbearing potential. (Women who have undergone hysterectomy, bilateral oophorectomy, bilateral tubal ligation or have been

without menses for 12 months and have LH, FSH and estradiol measurements within the post-menopausal range are considered to be of non-child bearing potential).

- Medical and concomitant medication history assessment
- (Remind patient of requirement for fasting blood sample on Day 0)

#### **Day 0 (Day of Treatment, Pre-Dose)**

On the day of dosing, prior to infusion, the following tests and procedures will be done:

- 12-lead ECG
- Assessment of ECOG performance status
- Medical history assessment
- Concomitant medications assessment
- Physical exam
- Body weight
- Temperature, vital signs, and SaO2
- Urinalysis with microscopic analysis
- CBC with differential and platelets
- Serum chemistry
- Serum lipids
- Patient takes thyroid protection medication
- Blood sample for pharmacokinetic (PK) analysis (one EDTA lavender top tube)
- Blood sample for biodistribution (one EDTA lavender top tube)

*See Laboratory and Biodistribution Manual, provided separately, for details about handling and processing PK and biodistribution samples.*

#### **Treatment**

- I-131-CLR1404 will be administered via a slow infusion of at least 10 minutes duration into a peripheral vein.
- Assessment of adverse events and concomitant medications

**See Nuclear Medicine and Radiopharmacy Instruction Manual for detailed information about dose preparation and infusion technique.**

#### **Day 0 (5 minutes Post Infusion)**

- 12-lead ECG
- Concomitant medications assessment
- Temperature, vital signs, SaO2
- Assessment of adverse events
- Blood sample for PK analysis (one EDTA lavender top tube)

#### **Day 0 (15 minutes Post Infusion)**

- Concomitant medications assessment
- Temperature, vital signs, and SaO2
- Assessment of adverse events
- Blood sample for PK analysis (one EDTA lavender top tube)
- Blood sample for biodistribution (one EDTA lavender top tube)

**Day 0 (15-35 minutes Post Infusion)**

- I-131-CLR 1404 whole body scans
- After scans are complete, begin 24 hour urine collection.

**See Appendix D, Whole Body Scanning and Dosimetry, as well as the Nuclear Medicine and Radiopharmacy Manual, for detailed instructions on scanning parameters.**

**Day 0 (30 minutes Post Infusion)**

- Concomitant medications assessment
- Temperature, vital signs, and SaO2
- Assessment of adverse events
- Blood sample for PK analysis (one EDTA lavender top tube)

**Day 0 (60 minutes Post Infusion)**

- 12-lead ECG
- Concomitant medications assessment
- Temperature, vital signs, and SaO2
- Assessment of adverse events
- Blood sample for PK analysis (one EDTA lavender top tube)
- Blood sample for biodistribution (one EDTA lavender top tube)

**Day 0 (4-6 hours Post Infusion)**

- 12-lead ECG
- Concomitant medications assessment
- Temperature, vital signs, and SaO2
- Assessment of adverse events
- Blood sample for PK analysis (one EDTA lavender top tube)
- Blood sample for biodistribution (one EDTA lavender top tube)
- I-131-CLR1404 whole body scans

**Day 1 (18-24 hrs)**

- 12-lead ECG
- Concomitant medications assessment
- Temperature, vital signs, and SaO2

- Assessment of adverse events
- Patient takes thyroid protection medication
- Blood sample for PK analysis (one EDTA lavender top tube)
- Blood sample for biodistribution (one EDTA lavender top tube)
- I-131-CLR 1404 whole body scans
- Start next 24 hour urine collection

**Day 2 (48 ± 6 hrs)**

- Concomitant medications assessment
- Temperature, vital signs, and SaO2
- Assessment of adverse events
- Patient takes thyroid protection medication
- Blood sample for PK analysis (one EDTA lavender top tube)
- Blood sample for biodistribution (one EDTA lavender top tube)
- I-131-CLR1404 whole body scans
- Start next 24 hour urine collection
- (Remind patient of requirement for fasting blood sample on Day 3)

**Day 3 (72 ± 6 hrs)**

- Concomitant medications assessment
- Temperature, vital signs, and SaO2
- Assessment of adverse events
- Serum lipids
- Patient takes thyroid protective medication
- Blood sample for PK analysis (one EDTA lavender top tube)
- Blood sample for biodistribution (one EDTA lavender top tube)
- I-131-CLR1404 whole body scans
- Optional SPECT imaging may be obtained between Days 3 and 14 at the Investigator's discretion
- Start next 24 hour urine collection, and give patient containers and instructions for collecting urine over the weekend at home

**Day 4 (96 hrs)**

- Patient takes thyroid protection medication
- Patient continues 24 hour urine collection at home.

**Day 5 (120 hrs)**

- Patient takes thyroid protection medication
- Patient continues 24 hour urine collection at home.

**Day 6 (144 ± 6 hrs)**

- 12-lead ECG
- Concomitant medications assessment
- Physical examination
- Temperature, vital signs, and SaO2
- Assessment of adverse events
- Urinalysis with microscopic analysis
- CBC with differential and platelet count
- Serum chemistry
- Patient takes thyroid protection medication
- Blood sample for PK analysis (one EDTA lavender top tube)
- Blood sample for biodistribution (one EDTA lavender top tube)
- I-131-CLR1404 whole body scans
- Optional SPECT imaging may be obtained between Days 3 and 14 at the Investigator's discretion
- Begin Days 7-10 and 11-14 urine collection; give patient containers and instructions for collecting and storing urine at home

**Days 7-13**

The following activities are conducted on each day:

- Patient takes thyroid protection medication
- Patient continues 24 hour urine collection at home

**Day 14 ± 1 Day**

The following procedures should be conducted at this visit:

- 12-lead ECG
- Body weight
- ECOG performance status
- Concomitant medications assessment
- Physical examination
- Temperature, vital signs, and SaO2
- Assessment of adverse events
- Urinalysis with microscopic analysis
- CBC with differential and platelet count
- Serum chemistry
- Patient takes thyroid protection medicine (completed after this dose)
- Blood sample for PK analysis (one EDTA lavender top tube)
- Blood sample for biodistribution (one EDTA lavender top tube)
- I-131-CLR1404 whole body scans

- Optional SPECT imaging may be obtained between Days 3 and 14 at the Investigator's discretion.
- Total urine, collection is completed at this visit

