## 5. STUDY DESIGN

### 5.1 STUDY SUMMARY

This will be a multi-center study evaluating dosimetry and safety for up to nine patients with refractory or relapsed advanced solid tumors who have failed standard therapy or for whom no standard therapy exists. Patients who are eligible will be infused with a single dose of 10 millicuries (mCi) of I-131-CLR1404. All patients will be prescribed thyroid protection medication to be taken 24 hours prior to injection of the study drug and for 14 days afterwards.

**Patients who withdraw from the study prematurely will be strongly encouraged to continue their thyroid protective medication for the full 14 days post infusion.**

Whole body imaging for dosimetry calculations will be performed at 15-35 minutes post injection; 4-6, 18-24, 48, 72, and 144 hours (Day 6) post injection, and on Day 14 post injection. At the Investigator's discretion, optional SPECT imaging may be obtained between Day 3 and 14 to further characterize the patient's tumor(s). Blood and urine will be collected for clinical laboratory evaluation pre-dose and on days 6, 14, 30 and 42. Blood will be drawn for evaluation of lipids pre-dose and at 72 hours post injection. Blood will be collected for pharmacokinetic analysis prior to dosing, and at 5, 15, 30, and 60 minutes; 4-6, 18-24, 48, and 72 hours; 6, 14, 30, and 42 days post infusion. Blood will be collected for radiologic biodistribution at pre-injection, 15 and 60 minutes, 4-6, 18-24, 48, and 72 hours; 6, 14, 30 and 42 days post dose. Patients will be asked to collect all of their urine for 14 days post injection in order to evaluate the urinary clearance of I-131-CLR1404. Patients will be monitored at each visit for adverse events and the use of concomitant medications.

Patients must have a refractory or relapsed advanced solid tumor and have a sufficient window of time to complete the washout period of 2 weeks if they have received standard therapy or 4 weeks if they have received experimental therapy, the dosimetry data acquisition (14 days), and the follow-up safety assessment period (4 weeks) prior to beginning another cycle of a therapeutic regimen. If, after 30 days on study the patient is not experiencing any drug-related toxicity, the patient can continue further treatment with a clinically appropriate non-investigational therapy, at the discretion of the Investigator.

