### **Thyroid Protection Premedication**

To protect the thyroid from any possible uptake of radioactive iodine, thyroid protection is required. Thyroid protective agents should be initiated at least 24 hours prior to, the day of, and for 14 days after administration of I-131-CLR1404. Premedication regimens vary, but they should include one of the following:

- Saturated solution of potassium iodide (SSKI) 4 drops orally t.i.d.
- Lugol's solution 20 drops orally t.i.d.
- Potassium iodide tablets 130 mg orally q.d.

**Patients should not receive I-131-CLR1404 if they have not yet received at least 3 doses of SSKI, three doses of Lugol's solution, or one 130 mg potassium iodide tablet (at least 24 hours prior to the infusion.).**

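### The visit list ends thyroid protection at a visit that may fall on Day 13, one day short of the 14 days stated in Sections 5.1 and 7.6

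*Protocol*

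**What the plan says.** Three parts of the Protocol say when thyroid protection ends.

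- **Duration in days.** Section 5.1 prescribes "thyroid protection medication to be taken 24 hours prior to injection of the study drug and for 14 days afterwards". Section 7.6, under the thyroid premedication heading, says "Thyroid protective agents should be initiated at least 24 hours prior to, the day of, and for 14 days after administration of I-131-CLR1404". Section 5.1 adds, in bold, that patients who withdraw early are to be "strongly encouraged to continue their thyroid protective medication for the full 14 days post infusion". Sections 7.2 and 7.4 repeat the 14 days for withdrawals.
- **Schedule footnote.** Footnote 7 to the table in Section 8.1 says "Patient takes thyroid protection medication each day on Days -24 hrs through Day 14".
- **Visit lists.** Section 8.2.2 has, for each of Days 7-13, "Patient takes thyroid protection medication". The next entry is headed Day 14 ± 1 Day and reads "Patient takes thyroid protection medicine (completed after this dose". It sets no condition that Day 14 has been reached.

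The ± 1 day window also appears in the schedule table and in Section 8.2.3.14, so a visit on Day 13 is permitted. Section 7.6 allows three regimens: two are taken three times a day (SSKI and Lugol's solution) and one once a day (potassium iodide tablets).

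**The concern.** Sections 5.1 and 7.6 fix the end of protection by time since infusion. The visit list fixes it by a visit whose date can move. The two agree when the visit is held on Day 14. They disagree when it is held on Day 13: that patient is finished according to the visit list and one day short according to Sections 5.1 and 7.6.

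The Protocol calls thyroid protection required, describes no other measure for the thyroid, and stresses the duration even for patients who leave the study. As written, a patient who withdraws is urged to complete 14 days, while a compliant patient seen on Day 13 is told that the course is over. The visit list is also the page that site staff are likely to work from on the day.

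The visit-list wording is loose in a second way. It speaks of a dose, not of a day. On a three-times-daily regimen the dose taken at the visit need not be the last one of that day.

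**Working it through.** No sample-size or other statistical formula is involved. The check is a count of days, with the infusion on Day 0.

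**Inputs**
- Stated duration: 14 days after the infusion (Sections 5.1 and 7.6).
- Status of Day 0: Section 7.6 names the day of administration separately, so the 14 days are Days 1-14.
- Visit window: Day 13 to Day 15 (Section 8.2.2, the schedule table, Section 8.2.3.14).
- End under the visit list: the dose at that visit.

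**Formula**
- Post-infusion days covered under the visit list = day number of the visit.
- Shortfall = 14 − day number of the visit, if positive.

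**Results**
- Visit on Day 14: 14 days covered, 14 − 14 = 0 short. The stated figure is reproduced.
- Visit on Day 13: 13 days covered, 14 − 13 = 1 day short, and 1/14 = 0.071, about 7%.
- Visit on Day 15: the visit falls after the 14 days, so it creates no shortfall.

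**Alternative count.** If Day 0 were one of the 14 days, a Day 13 visit would give Days 0-13, which is 14 days, and the conflict would vanish. Section 7.6 does not allow this, because it lists the infusion day in addition to the 14 days that follow.

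**Doses on the visit day.** On a three-times-daily regimen, if the dose at the visit is the first of that day, 3 − 1 = 2 doses remain. The visit list can be read as cancelling them or as meaning that protection ends with that day. The question arises on any visit date, Day 14 included. It does not arise for the once-daily tablet.

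**The case against.** The strongest reply is that nothing conflicts at the planned visit. Home dosing on Days 7-13 followed by the Day 14 dose gives the 14 days, and Sections 5.1 and 7.6 are explicit. A site that ended protection on Day 13 would depart from those sections even though the visit itself was in window. The error therefore needs both a Day 13 visit and a site that reads the visit list alone. This is right and limits the size of the point. It does not remove the point, because nothing in the Protocol tells a patient seen on Day 13 to go on.

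Footnote 7 is weaker support than it looks. The Day 14 column of the schedule table itself carries the ± 1 day window, so the footnote may mean that visit and agree with the visit list. The conflict rests on Sections 5.1 and 7.6. Likewise, the emphatic sentence about the full duration in Section 5.1 concerns patients who withdraw and is an encouragement.

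A reader might go further in two directions that the document does not support.

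- **Harm from residual I-131.** I-131 is still present on Day 13, so the missing day might seem to leave the thyroid exposed. But I-131 is also present on Day 14, where the Protocol itself ends protection, so its presence does not measure what one day costs. The Protocol's half-lives are the physical one for I-131 and a plasma one for a related compound. Neither gives the free iodide available to the thyroid, and no figure for release of iodide from the drug is stated.
- **Damage to the excretion data.** Urine collection ends at the same visit, which might suggest a dosimetry problem. Section 11.4 speaks of collection for up to 14 days, Section 8.2.3.13 allows it to stop after Day 6 if no radioactivity is measurable, and each interval's volume is measured and sampled for counting. No error in the dosimetry follows from the window.

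**Conclusion.** The inconsistency stands and is minor. The visit list gives 13 post-infusion days for a patient seen on Day 13, against 14 in Sections 5.1 and 7.6: one day, about 7% of the stated duration. In addition, the wording about the final dose is ambiguous for two of the three permitted regimens on any visit date.

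The day-count result assumes that the infusion day is not one of the 14, as Section 7.6 implies, and that the site follows the visit list. How many patients would be seen on Day 13 is not known; Section 6.1 expects up to nine in all. No clinical consequence of the missing day and no effect on the primary endpoints can be shown from the Protocol. No view is taken on which duration is right.

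**What to change.** The sponsor should reconcile the Day 14 ± 1 Day entry in Section 8.2.2 with Sections 5.1 and 7.6 and with footnote 7 in Section 8.1. The end of thyroid protection should be stated once, and the other passages should match it, so that a patient seen on any date in the window receives the same instruction. The text should also make clear how the final day is handled under a three-times-daily regimen. Which wording governs is for the sponsor to decide.

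The cost is negligible: an edit of about one line in the visit list, with matching wording elsewhere if needed. The edit adds no visit or test.

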### **Day 30**

- Concomitant medications assessment
- Assessment of ECOG performance status
- Physical exam
- Temperature, vital signs, and SaO2
- Assessment of adverse events
- Urinalysis with microscopic analysis
- CBC with differential and platelet count
- Serum chemistry
- Blood sample for PK analysis (one EDTA lavender top tube)
- Blood sample for biodistribution (one EDTA lavender top tube)

### **Day 42 (Final Visit)**

- Serum pregnancy test (if applicable)
- Concomitant medications assessment
- Assessment of ECOG performance status
- Physical exam
- Temperature, vital signs, and SaO2
- Assessment of adverse events
- Urinalysis with microscopic analysis
- CBC with differential and platelet count
- Serum chemistry
- Blood sample for PK analysis (one EDTA lavender top tube)
- Blood sample for biodistribution (one EDTA lavender top tube)

## **8.2.3 Clinical Assessments**

### **8.2.3.1 ECG**

A standard supine resting 12-lead electrocardiogram will be performed at screening, pre-infusion, 5 and 60 minutes post infusion, as well as 4-6 hrs, 18-24 hrs, 144 hrs, and 14 days post infusion. The screening ECG must be obtained within 7 days prior to infusion of I-131-CLR1404.

#### 8.2.3.2 *Serum Pregnancy Test*

A serum pregnancy test (if applicable) will be obtained at Day -1 or pre-treatment, and on Day 42 post infusion. Women who have undergone hysterectomy, bilateral oophorectomy, and bilateral tubal ligation or have been without menses for 12 months and have LH, FSH and estradiol measurements within the post-menopausal range are considered to be of non-child bearing potential

#### 8.2.3.3 *ECOG Performance Status*

Determination of the patient's performance status based on the ECOG rating scale will be made at screening, pre-treatment, and at Days 14, 30, and 42. The screening ECOG performance status must be determined within 7 days prior to infusion of I-131-CLR1404.

#### 8.2.3.4 *Medical History and Medication Review*

A thorough review of the patient's medical history, taking into account all recent and pertinent medical conditions including prior cancer treatment, will be performed during the screening phase of the study. All current and recent medications will be reviewed and recorded in the case report form. The medical history and medication review must be obtained within 7 days prior to the infusion of I-131-CLR1404.

#### 8.2.3.5 *Physical Exam*

A detailed physical exam, noting all abnormalities and sites of palpable neoplastic disease, will be performed during screening, pre-dose, and Days 6, 14, 30, and 42. The screening physical exam must be performed within 7 days prior to the infusion of I-131-CLR1404.

#### 8.2.3.6 *Temperature, Vital Signs and Oxygen Saturation*

Temperature, vital signs (pulse, supine blood pressure and respirations per minute) and oxygen saturation (measured with pulse oximeter) will be recorded at screening, pretreatment, 5, 15, 30, and 60 minutes post infusion, 4-6 hours post infusion, at each imaging visit, and at Days 30 and 42.

